### NPV Calculation

Nnegative = Z_0.025_^2^x (NPV(1 ‐ NPV))/W^2 ^ = 1.96^2^x (0.95(1 ‐ 0.95))/0.03^2^ = 203

### Assessments and procedures

The required assessments and procedures are outlined in Table 2. Eligible children undergo POCT in parallel to their standard ED care with no delay (Fig. 3). Residual specimens beyond what is needed for standard care is tested using the Hibergene LAMP-MD and the Samsung IB10 (BRAHMS) PCT.

**Table 2 Tab2:** PiC Study assessments

	In ED	Follow-up		
		4 h	0–24 h	Within 1 Month
Consent discussion	X	X	X	
Assessment of eligibility criteria	X			
POCT	X			
Laboratory assessments – routine bloods and throat swabs	X			
Notes review and CRF completion by member of research team			X	
Review of medical history by member of research team			X	
Qualitative interview conducted by TW				X

**Fig. 3 Fig3:**
[figure not shown]
Flow diagram for study proceduress

### Performing index tests - blood samples & throat swabs

POCT is performed by ED clinical staff, with bespoke training provided by the research team, and a training log maintained. Members of the research team are contactable to provide support as required. Index tests are performed as soon as possible, and are done prior to result of the reference standard test (Quantitative PCR) being available.

#### LAMP-MD

A throat swab taken as part of routine care is mixed in a sample buffer; a small aliquot of this (50 μl) is used, and the main sample is forwarded to the laboratory as per normal practice. Standard testing includes molecular testing for *N. meningitidis*, human enteroviruses, and a series of other viral targets using reference-laboratory real-time PCR methods. The aliquot drawn in the ED is analysed using the Hibergene LAMP-MD POCT test (giving positive/valid, negative/valid or invalid result) – Fig. 1.

#### Procalcitonin

0.5 ml of blood is taken from the samples collected as part of routine care. POCT PCT testing is done on this sample in the ED using the Samsung IB-10 analyser with a positive threshold level of > 1.93 ng/ml. If insufficient blood is obtained, then routine testing is prioritised. Routine blood testing includes WBC, CRP, coagulation screen, blood gas, and molecular testing for *N. meningitidis*, human enteroviruses, and other viral and bacterial targets (including *Streptococcus pneumoniae* and *Haemophilus influenzae*) using reference-laboratory real-time PCR methods – Fig. 2.

### Reference standards

In all cases of possible MD, blood and/or CSF is tested for *N. meningitidis* DNA using quantitative crtA TaqMan PCR using standard UK laboratory methods. The reference standard test is performed by staff blinded to the result of the index test. A positive reference standard test will be used to give a diagnosis of “confirmed MD”.

In cases where the diagnosis is unclear or where the child has been diagnosed as “probable MD” by the clinical team but where the reference standard test is negative a committee of clinicians will review the anonymised medical records blinded to results of POCT and decide if the case can be given the diagnosis of “probable MD”.

For other invasive bacterial infections, the reference standard test is positive culture or qPCR of bacterial pathogen from a sterile body site (blood/CSF) performed by staff blinded to the result of the index test.

### Case report form (CRF)

All children recruited to the study will have a standardised CRF completed by a member of the research team. Regular meetings will be arranged to ensure standardisation of data collection. Demographic data will be collected as will data pertinent to current CPGs. This includes, but is not limited to, vital signs, overall wellness, duration of illness, appearance and distribution of the rash, any spread of the rash over time (including the first 4 h in hospital). Data will be collected on investigations performed, treatments given, final diagnosis, length of stay and survival to discharge. Where data is unclear from the clinical record the researcher will collect additional information from the child’s parent and attending physician.

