#### Lamp md

LAMP-MD is a rapid molecular amplification test for the detection of all serogroups of *N. meningitidis* DNA. It can be performed in the ED on a bench top analyser and provides results within 30 min (Fig. 1). Initial testing has shown that LAMP-MD has superior sensitivity (0.89 [95%CI 0.72–0.96]) and specificity (1.0 [95%CI 0.97–1.0]) in diagnosing MD than traditional tests (C-reactive protein [CRP] and White Blood Cell counts [WBC]) recommended by NICE [10, 11]. The LAMP-MD test is now available commercially and is CE-IVD approved. The test performs equally well on blood samples and throat swabs, [10] with results available more quickly from throat swabs due to a shorter and simpler DNA extraction process.

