#### Approaching parents

A member of the research team will be notified of the participation of the child in the study and will approach the parent to seek consent as soon as possible after undergoing POCT (ideally within 24 h). In the majority of cases this will take place on a ward or in the ED. Consent will only be sought once the child is stable and following consultation with the clinical team caring for the child in line with best practice recommendations [15–17].

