### Potential benefits

For children admitted to hospital for IV antibiotics, there is no likelihood of personal benefit from participating in this study. However for enrolled children who would otherwise be discharged directly from the ED there is potential benefit, as the results of the LAMP-MD and PCT will be made available to the clinical team. Being enrolled in this study may therefore result in the child receiving lifesaving treatment that they would have otherwise not received, with guidance provided for clinicians on meaningful test cut-points. [10, 12].

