### Potential bias

As the clinical team are not blinded to the results of the index tests, there is an increased risk of bias in treatment. It was deemed ethically unacceptable to withhold these results from clinicians. However as our performance accuracy is primarily assessed laboratory tests we expect any bias to be minimized, with a residual risk remaining for cases which require a clinical decision as to the likelihood of MD in the context of negative laboratory tests. When this occurs bias will be minimized by ensuring the treating clinician is not part of this panel, with information taken solely from clinical notes. In addition the laboratory team performing reference tests will be blinded to index tests. This includes blood culture testing and qPCR for other invasive bacterial infections.

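### Guideline items may be recorded or clarified with knowledge of the LAMP and PCT results, a bias that the protocol's bias section does not recognise

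*Protocol article*

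**What the plan says.** - **Who records the guideline items.** Case report form (CRF): "All children recruited to the study will have a standardised CRF completed by a member of the research team". The items listed as relevant to the guidelines include vital signs, overall wellness, rash appearance and distribution, and "any spread of the rash over time (including the first 4 h in hospital". Final diagnosis goes on the same form.
- **When.** In Table 2 (Assessments and procedures) point-of-care testing is marked in the ED column. The row "Notes review and CRF completion by member of research team" is marked at 0–24 h.
- **How gaps are filled.** CRF section: "Where data is unclear from the clinical record the researcher will collect additional information from the child". The sentence goes on to name the parent and the attending physician as sources.
- **Who knows the results.** LAMP-MD "provides results within 30 min", and PCT takes 20 minutes. ED clinical staff run both tests. Under Potential benefits, "the results of the LAMP-MD and PCT will be made available to the clinical team". Potential bias confirms that the clinical team is not blinded.
- **Where blinding is stated.** It is stated for the reference laboratory and for the probable-MD committee (Reference standards; Potential bias).
- **What bias is acknowledged.** Potential bias mentions bias in treatment. It then relies on accuracy being assessed mainly by laboratory tests, "with a residual risk remaining for cases which require a clinical decision as to the likelihood of MD" when those tests are negative.
- **What is analysed.** Statistical analysis lists, as secondary, the sensitivity, specificity, NPV and PPV of existing guidance against qPCR, McNemar's test between guidelines and, where possible, the effect of adding point-of-care tests to the guidance.

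**The concern.** In the secondary analysis the guidelines are themselves index tests, and several of their inputs are clinical judgements. The protocol protects the point-of-care tests by running them before qPCR is known, and protects the laboratory and the committee by blinding. It states no protection for the guideline inputs. The reassurance in Potential bias fits LAMP and PCT but not an index test built partly on wellness and rash spread.

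Three outputs are exposed: the accuracy of each guideline, the McNemar comparison, and the estimate of what point-of-care testing adds. The last is the most direct. If knowledge of LAMP or PCT has shaped the guideline-alone classification, that classification is no longer a clean comparator. The abstract's Discussion also says the study will identify which guideline elements merit inclusion in later decision-rule work, and wellness and rash spread are among the elements most open to this influence.

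**Working it through.** **1. The protocol's own figure.** 1.96² × 0.95 × 0.05 / 0.03² = 202.75, rounded up to 203, as stated in NPV Calculation. It does not depend on the guideline items.

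**2. Sequence.** Results return 20–30 minutes after testing, which is done as soon as possible in the ED. Rash spread is followed for 4 h and the CRF is completed at 0–24 h. In the ordinary course the 4 h item cannot be complete before the result is known, and a later query to the attending physician goes to a member of the unblinded team. Vital signs and the rash at presentation may have been written down earlier; the article gives no entry times.

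**3. How close LAMP is to the reference.** Inputs from Lamp md: sensitivity 0.89 (0.72–0.96), specificity 1.0 (0.97–1.0). Prevalence from Sample size justification: 15% or lower. Agreement = prevalence × sensitivity + (1 − prevalence) × specificity.
- Point estimates at 15%: 0.15 × 0.89 + 0.85 × 1.0 = 0.9835 (kappa 0.93).
- Lower limits at 15%: 0.15 × 0.72 + 0.85 × 0.97 = 0.9325 (kappa 0.72). PPV = 0.108 / (0.108 + 0.0255) = 81%.
- Lower limits at 5% (assumed prevalence): PPV = 0.036 / (0.036 + 0.0285) = 56%.

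**4. How many children could be reclassified.** 300 × 0.90 = 270 children. At 15% prevalence, about 40 have MD and 230 do not. Prior guideline accuracy is from Current UK guidance (sensitivity: NICE 97%, NBL 100%; specificity: 50% and 82%).
- MD children missed by the guideline: NICE 0.03 × 40 = 1.2; NBL 0.
- MD children who are LAMP-negative, and so open to a milder description: 0.11 × 40 = 4.4.
- Guideline false positives: NICE 0.50 × 230 = 115; NBL 0.18 × 230 = 41.
- Weight of one MD child on sensitivity: 1/40 = 2.5 points. At 5% prevalence (about 14 cases) it is 1/14 = 7.1 points.

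**5. Illustration.** Assume a fraction f of guideline classifications that disagree with LAMP drift towards it, and that guideline and LAMP errors are independent. The documents give no value for f; 5–20% is an assumption. With LAMP specificity 1.0:
- Specificity after drift = Sp + (1 − Sp) × f
- Sensitivity after drift = Se + (1 − Se) × 0.89 × f − Se × 0.11 × f

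| | Prior | f = 5% | f = 20% |
|---|---|---|---|
| NICE specificity | 50% | 52.5% | 60% |
| NBL specificity | 82% | 82.9% | 85.6% |
| NICE sensitivity | 97% | 96.6% | 95.4% |
| NBL sensitivity | 100% | 99.5% | 97.8% |

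If only upward drift occurred in LAMP-positive children, NICE sensitivity would reach 97.1–97.5% and NBL would stay at 100%. If specificity drift also required a low PCT (specificity 0.74), the f = 20% figures would be 0.50 + 0.50 × 0.74 × 0.20 = 57.4% for NICE and 0.82 + 0.18 × 0.74 × 0.20 = 84.7% for NBL. In the table the specificity gap between guidelines narrows from 32 points to 30.4 (82.9 − 52.5) or 25.6 (85.6 − 60).

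**The case against.** The strongest reply has four parts.

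- **Prospective, standardised collection.** Data are described as collected prospectively, on a standardised CRF with regular standardisation meetings, and late abstraction does not make the observations late. This stands for items charted at presentation. It does not cover 4 h rash spread or answers given by the physician afterwards.
- **Conditional queries.** Parent and physician are asked only where the record is unclear, and whether parents know the results is not stated. This stands, and it limits how often that route operates.
- **A condensed article.** The full protocol or CRF manual may mask the abstractor or order the items. That absence alone is not held against the plan. Masking the abstractor would still leave inputs written or clarified by clinicians who are expressly unblinded, and the article's own bias argument does not extend to guideline inputs.
- **Disclosure.** The unblinding is declared and justified ethically. True, but the consequence drawn from it is confined to treatment and to cases needing a clinical decision.

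A reader might also infer that guideline accuracy is in effect measured against a known reference. The documents do not support that. qPCR is run blind, whether its result is back at CRF completion is not stated, and LAMP comes close to the reference on the point estimates but less so at the interval limits.

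**Conclusion.** The concern holds as a risk of bias in a secondary objective. Knowledge of LAMP and PCT can enter the guideline inputs under the procedures as written, and the reasoning in Potential bias does not cover the guideline accuracy, McNemar and added-value analyses. The co-primary accuracy of LAMP and PCT and the sample size are unaffected.

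Size and direction cannot be read from the documents. Specificity may be more exposed than sensitivity, since far more children are guideline false positives than guideline misses. The illustrative shifts rest on an assumed 5–20% drift, on LAMP's point estimates and on pre-vaccine guideline figures; the protocol itself says current guideline performance is unknown.

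Two stronger readings are tempting. One is that hindsight must raise guideline sensitivity. It need not, because LAMP-negative MD children could be described more mildly. The other is that one or two recoded children would reverse the order of NICE and NBL. On the quoted 97% and 100%, upward recoding could at most produce a tie.

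**What to change.** 1. Have the research team complete the guideline items on the CRF, and assign guideline status, before opening point-of-care, qPCR or final-diagnosis results.
2. Flag each item's source (notes, parent, physician) and whether it was recorded or clarified after the point-of-care result.
3. Keep the full guideline, including 4 h rash spread, as the main analysis. Add a sensitivity analysis that excludes flagged items or restricts to those not flagged. Making pre-result items the main analysis would drop the 4 h input and evaluate a truncated guideline.
4. Amend Potential bias to list the guideline evaluation, including the McNemar and added-value analyses, among the outcomes at risk.

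The cost is slight extra CRF work and one additional analysis. No result is withheld from clinicians. Ordering the CRF removes the abstractor's knowledge but not the clinicians', so the flags remain necessary, and some items such as 4 h spread will always carry one.

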### Interviews with parents and clinicians

The study includes interviews with (*n* = ~ 20) parents and (*n* = ~ 5–10) clinicians involved with recruitment and consent processes to explore their views on RWPC in this study.

During the consent process, parents are asked whether they consent to a qualitative telephone interview, which takes place within one month of their child’s discharge from hospital. All parents are invited to consent for a qualitative interview, including those who decline the use of their child’s information in the study. Interviews will be conducted until data saturation is reached [14].

All interviews with parents and clinicians will be conducted by TW. Any distress during the interviews will be managed with care and compassion and participants will be free to decline to answer any questions that they do not wish to answer or to stop the interviews at any point. Consent for audio recording will be sought. If consent is not provided then the interview will not continue.

### Research without prior consent (deferred consent)

Informed consent is a process initiated prior to an individual agreeing to participate in a study and continues throughout the individual’s participation. When consent is deferred, an individual is agreeing to the use of data that had already been collected for study purposes and for continued participation in the study [15, 16]. Research without prior consent in children has been shown to be appropriate and well accepted by parents when conducted in emergency situations and when information and opportunities for consent are offered at an appropriate time [15, 16]. In the PiC study we intend to assess the performance of rapid bedside tests in the diagnosis of a life-threatening emergency. In this situation, every minute counts and it is therefore not possible or appropriate to delay testing whilst consent is obtained (even for a few minutes). Following testing parents will be approached at the earliest appropriate opportunity and ideally within 24 h.

#### Approaching parents

A member of the research team will be notified of the participation of the child in the study and will approach the parent to seek consent as soon as possible after undergoing POCT (ideally within 24 h). In the majority of cases this will take place on a ward or in the ED. Consent will only be sought once the child is stable and following consultation with the clinical team caring for the child in line with best practice recommendations [15–17].

#### Approaching parents in the ED

Not all children with a fever and NBR are admitted. If the child appears well the clinician may choose to perform investigations and observe the child in the ED. Following a period of observation (typically 4–6 h) the child may be discharged if they appear well and testing is reassuring. In this group, we intend to seek consent prior to discharge. Before approaching the family in the ED, the researcher checks with clinical staff that the child is stable and timing is appropriate. An ED clinician explains the nature of the study to the parent and invites them to discuss the study with the researcher.

Some children will be discharged before consent can be obtained. In this instance, an ED clinician will contact the parent by telephone (maximum of 3 attempts) to explain the study and invite parents to discuss the study with a researcher, who then explains the reasons for RWPC, and how to opt in or out of the study. The parent is sent a patient information sheet (PIS), consent form and follow up letter. This letter explains the study, reasons for RWPC, how to opt in or out of the study, and provide contact details for the research team. If after 4 weeks there is no response, a follow up letter, PIS, and consent form are sent to the family. This explains the study, reasons for RWPC, how to opt in or out, and provides contact details for the research team. This letter also confirms that if no consent form is received within 4 weeks then the participant’s data will not be included in the study.

#### Approaching parents on the wards

The research team is notified of enrolment and approaches the parent to seek consent as soon as possible after undergoing POCT (ideally within 24 h). Based on CONNECT best practice guidance for performing RWPC the researcher checks with the clinical team that the participant is stable and that timing is appropriate before approaching the parent on the ward [16]. If the participant’s condition has not stabilized additional time will be allowed [16]. A member of the ward team explains the nature of the study and invites the parent to talk with the researcher.

#### Death prior to consent being sought

This will be rare, but almost certainly will occur. When a participant dies before consent has been sought TW will obtain information from colleagues and establish the most appropriate practitioner to notify parents of the research involvement.

Consent can be sought from parents following the death of their child and prior to the parent’s departure from the hospital. However, it is at the discretion of the clinical staff to determine if this is appropriate for each individual family. It maybe that it is not appropriate for consent to be obtained prior to discharge [15, 16].

Following the death of a child at the RBHSC it is routine practice to invite the parents to a meeting with the consultant in charge of their child’s care. This usually takes place 4–6 week after death. At this meeting, the consultant will be asked to explain the PiC study, reasons for RWPC, how to opt in or out, and provide contact details for the research team.

Following the meeting, 4 weeks is allowed for the family to contact the research team. If no contact is made then a personalised letter including the PIS and consent form is sent to the family. This explains the study, reasons for RWPC, how to opt in or out, and provides contact details for the research team. If after 4 weeks after sending the initial letter to the bereaved family, there is no response, a follow up letter along with the parent representative information sheet and consent form will be sent to the bereaved family. This second letter will explain the study, reasons for research without prior consent (deferred consent), how to opt in or out of the study and provide contact details if parents wish to discuss the study with a member of the research team (either in person or by telephone). In addition, this letter will also confirm that if no consent form is received within 4 weeks of the letter being sent then the participant’s data will NOT be included in the study.

#### Deferred consent declined/not obtained

If RWPC is declined or not obtained the child’s data will not be included. TW will maintain a record of all instances of declined/not obtained consent.

#### Withdrawal of consent

Consent may be withdrawn at any time without providing a reason and without being subject to any resulting detriment. The rights and welfare of the patients will be protected and the quality of medical care will not be adversely affected if they decline to participate in the study. TW will maintain a record of all those that withdraw consent to participate in the study.

*Research Ethics Committee (REC) and Institutional Review Board (IRB) opinion*

*The Northern Ireland REC and the Belfast Trust IRB have both reviewed the PiC protocol and provided a favorable outcome including the use of research without prior consent (deferred consent) as described above (Project ID 224660).*

### Statistical analysis

In keeping with the objectives we will report:

Primary:The diagnostic accuracy of POCT for (i) *N. meningitidis* DNA and (ii) PCT in the diagnosis of early MD against the reference standard (qPCR) for *N. meningitidis* DNA in blood/CSF). The sensitivity, specificity, NPV and PPV will be reported.The diagnostic accuracy of POCT for *PCT* in the diagnosis of early invasive bacterial infection against the reference standard of positive culture from a sterile site (blood/CSF). The sensitivity, specificity, NPV and PPV will be reported.

Secondary:The diagnostic accuracy of existing UK guidance in the diagnosis of early MD against the reference standard qPCR) of blood/CSF. The sensitivity, specificity, NPV and PPV will be reported. McNemar’s test will be performed to determine the significance in performance of different guidance. Where possible the effect of incorporating POCT into existing guidance will be explored and reported in term of sensitivity, specificity, NPV and PPV.Report on the aetiology of NBRs in children with a feverish illnessThe epidemiology of the population of children who present with fever and a NBR

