## Methods/design

As a diagnostic accuracy study our Petechiae in Children (PiC) study adheres to the STARD criteria for the reporting of diagnostic accuracy studies [13]. The gold standard test against which our outcomes are measured is quantitative PCR (qPCR) for *N. meningitidis* DNA in a sterile body site (blood or CSF). Or confirmation of an invasive bacterial infection through positive culture or qPCR of a bacterial pathogen.

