### Objectives

The co-primary outcomes are the diagnostic accuracy (sensitivity, specificity, positive predictive value, and negative predictive value) of:POCT for (i) *N. meningitidis* DNA and (ii) PCT in the diagnosis of MD in children with fever and NBRPOCT for *PCT* in the diagnosis of Invasive bacterial infection

Secondary objectives:Evaluate the performance accuracy of existing CPGs in identifying MDEvaluate cost-effectiveness of available diagnostic testing strategiesExplore views of (i) families and (ii) clinicians on research without prior consent (RWPC) using qualitative methodologyReport on the aetiology of NBRs in children with a feverish illness

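### The invasive bacterial infection co-primary has two conflicting case definitions: the analysis section drops both the pathogen requirement and qPCR

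*Protocol article*

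**What the plan says.** The Objectives section of the protocol article makes the accuracy of point-of-care PCT "in the diagnosis of Invasive bacterial infection" a co-primary outcome. Three places say what counts as a case:

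- Methods/design: "Or confirmation of an invasive bacterial infection through positive culture or qPCR of a bacterial pathogen".
- Reference standards: "the reference standard test is positive culture or qPCR of bacterial pathogen from a sterile body site (blood/CSF".
- Statistical analysis: "in the diagnosis of early invasive bacterial infection against the reference standard of positive culture from a sterile site (blood/CSF".

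The first two accept culture or qPCR and name a bacterial pathogen. The third accepts culture only and names no organism.

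Reference standards also sets up a committee of clinicians who review records without sight of the point-of-care results. Its stated output is to "decide if the case can be given the diagnosis of “probable MD", which concerns meningococcal disease (MD). No role is stated for it in judging culture isolates or IBI status. A PCT result is read "with a positive threshold level of > 1.93 ng/ml".

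**The concern.** Statistical analysis is the only section that states how the IBI co-primary will be computed, so its wording is the one an analyst would most readily follow. It departs from the other two sections in two ways.

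1. **No pathogen requirement.** A child with a self-limiting viral illness, a low PCT and a skin commensal in a blood culture would be an IBI case that PCT missed. True cases are likely to be few, so a handful of such children could be a large share of the diseased group.
2. **No qPCR.** A child with a bacterial pathogen found by qPCR but a negative culture would be analysed as free of IBI. A high PCT in that child would be a false positive, and a low PCT a true negative.

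Clinicians see the index results as they arise (Potential bias section). With two definitions in print, the choice between them could be made after PCT results are known. The study stresses rule-out, so an avoidable shift in sensitivity or NPV matters.

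**Working it through.** **Side by side**

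| Section | Culture | qPCR | Pathogen named |
|---|---|---|---|
| Methods/design | yes | yes | yes |
| Reference standards | yes | yes | yes |
| Statistical analysis | yes | no | no |

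**The plan's own figure.** NPV Calculation: 1.96² × 0.95 × 0.05 / 0.03² = 202.75, rounded up to 203. This reproduces. It refers to children negative on both tests, so it is context here and not the IBI analysis itself.

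**Inputs for the contamination illustration**

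- Analysed: 300 recruited less 10% refusal and dropout = 270 (Sample size justification).
- Prevalence: 15%, the planning ceiling in the same section, and 5% as an assumed lower value. Applying the ceiling to IBI is an assumption.
- PCT sensitivity 0.89 and specificity 0.74 (95% CI 0.40 to 0.92): from the Background subsection on procalcitonin, where they are given for early MD. Their use for IBI is an assumption.
- Contamination: a share c of children without IBI has a contaminated culture. The documents give no rate, so 1% to 5% is assumed.
- Contaminated children are PCT-positive at 1 − 0.74 = 0.26, as other uninfected children are.

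**Formulas.** Let D be true cases, N₀ = 270 − D, and C = c × N₀.

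- Sensitivity = (0.89 D + 0.26 C) / (D + C)
- NPV = 0.74 (N₀ − C) / [0.74 (N₀ − C) + 0.11 D + 0.74 C]

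**15% prevalence, c = 2%.** D = 40.5, N₀ = 229.5, C = 4.59.

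- Sensitivity = (36.045 + 1.193) / 45.09 = 0.826
- NPV = 166.43 / (166.43 + 4.455 + 3.397) = 0.955, against 169.83 / 174.285 = 0.974 with no contaminants

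**5% prevalence, c = 2%.** D = 13.5, N₀ = 256.5, C = 5.13.

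- Sensitivity = (12.015 + 1.334) / 18.63 = 0.717
- NPV = 186.01 / (186.01 + 1.485 + 3.796) = 0.972, against 189.81 / 191.295 = 0.992

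| Contamination | Sens., 15% | NPV, 15% | Sens., 5% | NPV, 5% |
|---|---|---|---|---|
| 0% | 0.890 | 0.974 | 0.890 | 0.992 |
| 1% | 0.856 | 0.965 | 0.789 | 0.982 |
| 2% | 0.826 | 0.955 | 0.717 | 0.972 |
| 3% | 0.798 | 0.945 | 0.661 | 0.962 |
| 5% | 0.751 | 0.926 | 0.583 | 0.943 |

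Specificity stays at 0.74. PPV rises slightly (at 2%: 0.377 to 0.389, and 0.153 to 0.170). With specificity at its confidence limits of 0.92 and 0.40, sensitivity at 2% contamination is 0.81 and 0.86 at 15% prevalence, and 0.67 and 0.81 at 5%.

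**Dropping qPCR.** Suppose m true cases are found by qPCR only and PCT detects them at 0.89. Moving them to the non-IBI group adds 0.89 m false positives and 0.11 m true negatives, and removes the same numbers of true positives and false negatives. Specificity becomes (0.74 N₀ + 0.11 m) / (N₀ + m), which is below 0.74. PPV falls and NPV rises. Sensitivity is unchanged in expectation but rests on fewer cases. The documents give no basis for m, so no size is attached. On NPV and PPV this works against the contamination effect, and nothing suggests that the two would cancel.

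**The case against.** The strongest reply is that Reference standards is where the protocol defines the standard, and on its natural reading a contaminant is not a bacterial pathogen. The Statistical analysis section may simply restate that definition in short form, and nothing there says it overrides the fuller one. This largely stands. A reader might infer that the study will score every positive culture as disease, and the document as a whole does not support that. The reply does not remove the conflict. The short form changes the case definition in two respects, and in the fuller text the pathogen qualifier could be read as attaching to qPCR alone.

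A second reply is that an organism list and a named classifier belong in a full protocol, analysis plan or laboratory procedure, none of which is shown. That stands too: their absence from an article is not an error.

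A third concerns size. The contamination rate is assumed, PCT accuracy is borrowed from MD, and a rate applied to all children without IBI presumes that nearly all have a culture. The routine blood tests listed under the index-test procedures do not name blood culture, although Potential bias mentions it. Fewer cultures would mean fewer contaminants. NPV also stays at or above 0.95 in most of the scenarios. It falls below that value only at 15% prevalence with 3% contamination or more, and at 5% prevalence with 5%. So a reader should not infer that the NPV planning value would be missed.

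**Conclusion.** The point holds as a conflict between sections: one co-primary outcome has two case definitions, and the analysis section carries the one without a pathogen requirement and without qPCR. Applied literally, that version would bias PCT sensitivity and NPV downward through contaminated cultures and would misclassify qPCR-only cases as non-IBI.

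At an assumed 2% contamination, about five children, sensitivity would lose about 6 points at 15% prevalence and about 17 at 5%, and NPV about 2 points at either. The direction holds whenever contaminated children are PCT-positive less often than true cases. The size depends on the assumed contamination rate, prevalence and PCT accuracy. If analysts apply the Reference standards definition, read as requiring a pathogen for culture as well as for qPCR, neither error arises. The documents therefore show an unresolved definition that should be settled before PCT results are linked to outcome, and not an established bias.

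**What to change.** 1. In Statistical analysis, replace the IBI reference standard with the one in Reference standards: a bacterial pathogen identified in blood or CSF by culture or by qPCR. In Reference standards and Methods/design, make explicit that the pathogen requirement applies to culture as well as to qPCR.
2. Extend the existing committee's remit so that isolates of doubtful significance are classified as pathogen or contaminant without sight of PCT.
3. Report the any-positive-culture definition as a sensitivity analysis, so that readers can see whether the choice matters.

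The cost is a sentence or two of text and committee review of what is likely to be a handful of isolates. The small downside is some judgement on those isolates, which blinding to PCT keeps from favouring either result.
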